### Standard treatment pathway

Patients enrolled into this study will follow standard operative care in line with each institution’s routine clinical practice, the only exception being the surgical approach as directed by the randomisation outcome.

### Allocated interventions

A total of 60 patients with tibial shaft fractures will receive one of two intramedullary nailing interventions:Infrapatellar nail entry: access to the tibia in all IPN approaches will be standardised using the medial parapatellar approach, as is the department standardSuprapatellar nail entry: access to the tibia in all SPN approaches will be standardised using a midline quadriceps incision

All nails in this study will be Stryker T2 Alpha nails (Stryker Corporation, Kalamazoo, MI, USA). Both interventions will be performed by consultant surgeons or senior registrars in training familiar with the procedures. Participants will receive identical preoperative and postoperative treatment in both groups according to the standard protocol of the treatment centre.

### Participant flow timeline

The timeline for participant involvement in the trial is detailed in Fig. 1. Following randomisation, baseline patient assessment will be completed using an online form (note: this data is not affected by the randomisation allocation). Surgery will proceed at the earliest available opportunity in line with each hospital’s routine clinical practice. Operative information will be recorded using an online form. Recruitment, medical, and surgical data collection will occur at the Royal Adelaide Hospital and The Queen Elizabeth Hospital. Follow-up appointments will be scheduled such that medical imaging, clinical reviews, and gait laboratory assessments coincide. The first clinical review will occur at the treating institution, with all subsequent appointments at the Clinical Research Facility at The University of Adelaide. At each follow-up, patients will present for medical imaging at a diagnostic imaging practice (lateral and anteroposterior radiographs at all follow-ups; magnetic resonance imaging (MRI) at 6 and 12 months); followed by clinical examination with an orthopaedic and trauma specialist; finally, PROMS will be collected using an online form and gait laboratory assessments conducted at the Clinical Research Facility, Adelaide Health and Medical Sciences Building (all follow-ups except 6 weeks). At the conclusion of the gait laboratory assessments, participants will be provided a wrist-worn activity monitor to be returned after 7 days with a reply-paid envelope.

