### Primary clinical outcome measure

The primary clinical outcome measure for the pilot RCT is the incidence of AKP at 12-months follow-up. To assess AKP, participants will be asked to answer the following questions:

1. Do you experience any pain in the knee of the leg that was operated on? Yes/No

2. Was this pain present only after surgery and not beforehand? Yes/No

3. Is this pain located over the front of your knee? Yes/No

If patients answer yes to all questions, their pain will be regarded as postoperative AKP.

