#### Clinical assessment

At each follow-up, a clinician will assess lower extremity function including a general clinical assessment of tenderness, swelling, and range of motion, and record the Knee Society Score [44] (KSS). The KSS is a widely used system to score the function of the knee, comprising two parts: (1) the Knee Score (KS-KS) and (2) the Function Score (KS-FS). The scores range from 0 to 100; a higher score is equivalent to a better outcome. The Minimal Clinically Important Difference (MCID) for the KS-KS ranges from 5.3–5.9 points and for the KS-FS from 6.1–6.4 points [45].

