### Sample size

This study has been designed as a pilot study to determine the feasibility of a large-scale RCT. Therefore, no sample size calculation was performed. Based on the number of fractures in a year at the recruitment sites, we aim to recruit a total of 60 patients; allowing for some loss to follow-up, should enable 25 patients to complete follow-up assessments from each group (SPN and IPN), which is in-line with sample size recommendations for pilot studies [72].

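### Self-reported knee pain, probably including the primary anterior knee pain (AKP) items, is scheduled after an unblinded knee examination and in no fixed order with the kneeling, squatting and hop tests

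*Protocol article*

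**What the plan says.** All references are to the protocol article.

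- **Visit order.** Participant flow timeline puts imaging first and the specialist's examination second. The last step reads: "finally, PROMS will be collected using an online form and gait laboratory assessments conducted at the Clinical Research Facility". Patient-reported measures (PROMs) and the gait laboratory share this last step, and neither is placed before the other.
- **Content of the examination.** Clinical assessment describes, at each follow-up, a "general clinical assessment of tenderness, swelling, and range of motion", plus the Knee Society Score.
- **Blinding.** Randomisation and blinding states that patients, surgeons and researchers all know the allocation, because the scars lie at different sites.
- **Primary clinical outcome.** "The primary clinical outcome measure for the pilot RCT is the incidence of AKP at 12-months follow-up". The section continues: "To assess AKP, participants will be asked to answer the following questions". The first item begins "Do you experience any pain in the knee of the leg that was operated on" and the third is "Is this pain located over the front of your knee? Yes/No". Three yes answers make a case. No recall window, mode or position in the visit is given.
- **Mode of capture.** Data management says that all questionnaire data except the Knee Society Score and the sleep logs are captured electronically.
- **Laboratory tasks.** Performance based outcome measures lists upright and flexed kneeling, squatting, a hop test and step tests.
- **Use of the AKP label.** Exploratory clinical outcomes judges the new tool on how well it separates participants with AKP from those without.

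**The concern.** Self-report of pain is best taken before anyone presses, moves or loads the joint. Here the stated order is the reverse for the examination and open for the laboratory tasks. Three features make the AKP items sensitive to this if they are asked at that point:

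1. The threshold is any pain at all, in the present tense. By contrast, the pain visual analogue scale asks about usual pain over the last week.
2. Pain evoked on the day could also satisfy the second item (not present before surgery) and, if it is at the front, the third.
3. Background and rationale itself reports that kneeling causes the most severe knee pain and worsens existing pain in 60% of cases.

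Two uses of the data are at stake. The AKP rates by arm are meant to inform the full trial's design. The new tool is to be assessed with performance tests done on the same day as the AKP answer. If those tests can influence the answer, part of the apparent discrimination could come from the visit order.

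**Working it through.** **The plan's own figures.** No figure on this point is wrong. The Discussion gives 1080 patients for 53% free of AKP in both groups, a 10-point margin, a two-sided 90% confidence interval and 90% power:

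n per arm = 2 × 0.53 × 0.47 × (1.645 + 1.645)² / 0.10² ≈ 539.2, rounded up to 540, so 1080 in total. It reproduces exactly. It matters here only as the source of the 47% AKP rate and the 10-point margin used for scale. Sample size plans 60 enrolled and 25 completers per group.

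**Does the stated order reach the AKP items?**

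| Step | What the text supports |
|---|---|
| PROMs come after the examination | Stated (Participant flow timeline) |
| The examination includes tenderness and range of motion | Stated (Clinical assessment) |
| No blinding | Stated (Randomisation and blinding) |
| AKP items are captured electronically | Follows if they count as questionnaire data (Data management) |
| AKP items are on the same online form | Inferred: it is the only electronic patient self-report step described at follow-up, but the items are not among the instruments listed under PROMs |
| PROMs come before or after the kneeling and hop tests | Not stated |

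For the listed PROMs that concern the knee, the order relative to the examination is therefore a stated rule. For the AKP items it is a fair inference.

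**Scale, on assumed values.** The documents give no rate at which examination or testing changes an answer. Let f be the share of AKP-free patients whose answer turns to yes, with a true AKP rate of 0.47.

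- Same f in both arms: observed rate = 0.47 + 0.53f. For f = 0.05, 0.10 and 0.20 this gives 0.4965, 0.523 and 0.576.
- A true difference shrinks by the factor (1 − f). An assumed 20-point difference becomes 18 points at f = 0.10 and 16 points at f = 0.20.
- f higher in one arm by 0.10 or 0.20: spurious difference = 0.53 × 0.10 = 5.3 points, or 0.53 × 0.20 = 10.6 points.
- One changed answer among 25 in an arm: 1/25 = 4 points.

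For comparison, the 95% half-width for the risk difference at 25 per arm is 1.96 × √(0.47 × 0.53 × 2/25) = 27.7 points. In the pilot, sampling error exceeds any of these shifts. They matter more if the procedure is carried into a full trial with a margin near 10 points.

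**The case against.** The strongest case against is that most of the chain is inference. The AKP items are not placed in the visit, and the missing figure and table may place them. The sentence on visit order happens to name PROMs before the laboratory. The first item can be read as asking about habitual pain, and the second ties it to the time since surgery, so brief tenderness on palpation is not clearly what is being asked. Both arms have the same examination. Patients know their allocation anyway, so reordering would not remove differential reporting. The trial's primary objective is feasibility, and clinical analyses are declared exploratory.

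Much of this stands, and it limits the weight of the point. It does not remove the stated order: PROMs follow the examination. Nor does it supply a position for the primary clinical outcome.

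Four stronger readings are tempting and should not be drawn:

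- **That the AKP answer comes last.** The text does not place it, and PROMs share the final step with the laboratory.
- **That the outcome is lost when a visit is missed.** No section says so. The form is online, and Participant retention provides contact by phone, email or letter. What is absent is an explicit route for remote completion, which an article may leave to the full protocol. The expectation that recruiting 60 "should enable 25 patients to complete follow-up assessments from each group" concerns follow-up in general, so it gives no completeness figure for AKP at 12 months.
- **That the arms are biased against each other.** The incisions differ and the Discussion names different structures at risk, so unequal provocation is possible. Nothing in the document shows it.
- **That the new tool's validation is circular.** That would require the AKP items to follow the laboratory tasks, and the order is open.

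**Conclusion.** The point holds in a limited form. Knee self-report by PROM is scheduled after an unblinded examination that includes tenderness and range of motion, and in no stated order with provocative laboratory tasks. The primary clinical outcome probably shares that position. The answers may therefore be coloured by the visit, and the AKP label may not be independent of the tests used to build the new tool.

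The size and any difference between arms are unknown. The 5.3- and 10.6-point figures are illustrations that rest on assumed provocation rates and the 47% AKP rate quoted in the Discussion. The conclusion about AKP also assumes that its items are on the online form; if Fig. 1 or Table 1 shows otherwise, it narrows to the listed PROMs. Not every PROM is equally exposed, since the pain scale has a one-week window. This is a low-cost improvement of modest weight. It changes no sample size and no feasibility criterion.

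**What to change.** In Participant flow timeline, and in Primary clinical outcome measure where the items are defined:

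1. State that the AKP items and PROMs are completed on the visit day, on arrival, before the clinical examination and the gait tasks.
2. Record pain felt during the kneeling tests as a separate item, never as the AKP answer.
3. If the visit is missed, obtain the AKP items and PROMs by online link or phone, using the contact routes already described under Participant retention.

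The cost is a small change in visit logistics. Completing the forms on arrival keeps the same-day pairing with the biomechanical data that the tertiary objective needs. Remotely completed forms will have no paired laboratory data, so they can serve the comparison of AKP by arm but not the development of the tool.

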**Fig. 1 Fig1:**
[figure not shown]
Patient flow diagram. TS, tibial shaft; SPN, suprapatellar nailing; IPN, infrapatellar nailing; AP, anteroposterior; PROMS, patient-reported outcome measures; MRI, magnetic resonance imaging

### Participant retention

In order to maximise participant retention, patients will be instructed on the importance of attending all follow-up time-points. All appointments will be made in order to minimise the time-burden on the participants, i.e. scheduling imaging, clinical reviews, and gait laboratory sessions consecutively. Patients will be contacted primarily by phone and email, or mailed letters if contact is unsuccessful. Patients will be reminded of all follow-up sessions.

## Outcomes

### Feasibility outcomes

The primary objective of this study is to determine the feasibility of a larger scale RCT. Feasibility of a larger scale RCT will be determined by assessing the enrolment and retention rates, compliance with questionnaires and assessment procedures, and the occurrence of any adverse events. In the occurrence of any adverse events, the causality of the event in relation to the intervention will be assessed according to the National Health and Medical Research Council guidelines [43].

### Primary clinical outcome measure

The primary clinical outcome measure for the pilot RCT is the incidence of AKP at 12-months follow-up. To assess AKP, participants will be asked to answer the following questions:

1. Do you experience any pain in the knee of the leg that was operated on? Yes/No

2. Was this pain present only after surgery and not beforehand? Yes/No

3. Is this pain located over the front of your knee? Yes/No

If patients answer yes to all questions, their pain will be regarded as postoperative AKP.

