### Trial design

This study is designed as a prospective, parallel group pilot RCT aiming to compare the results of SPN versus IPN for tibial shaft fractures during the first 18 months after surgery. Randomisation will be computer-generated, restricted by stratification, and will be carried out in a 1:1 manner. Randomisation will be stratified by age (< 40/≥ 40) and patient gender.

For every tibial shaft fracture patient enrolled in the RCT, we aim to recruit a healthy, case-matched volunteer from the general population to generate a normative reference dataset. The healthy cohort of volunteers will be case-matched by considering age, sex, height, and body mass, and screened for eligibility over the phone.

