### Exploratory clinical outcomes

The tertiary objective of this study is the development of novel outcome measures specific to IM nailing of tibial shaft fractures from a series of performance-based and patient-reported outcomes captured in the pilot RCT. The successful development of the new tool using a combination of PROMs and PBOMs will be assessed on its ability to differentiate participants with and without AKP.

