### Protocol deviations

Patients that undergo nail removal will be asked to be followed up for an additional 18 months after nail removal. Indications for nail removal may include patient preference, knee pain, and infection [71].

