## Discussion

This protocol describes the design of pilot randomised controlled trial investigating the influence of SPN vs IPN on AKP after intramedullary nailing of tibial shaft fractures. In the last 10 years, studies have shown SPN increases accuracy of the nail entry point to the tibia [12], improves insertion angles [74], and is associated with good alignment rates [5, 13]. IPN has been associated with higher rates of malalignment [6, 75–77] in part because the flexed knee required for IPN can lead to extension of the proximal fracture fragment, making reduction difficult [75]. Additionally, the relatively easier reduction and positioning provided by SPN is associated with reduced fluoroscopy time [8, 78, 79]. The major drawback of SPN is concerns regarding the articular approach [14, 80–82] and permanently decreased quadriceps strength resulting from nail entry [80]. However, MRI and arthroscopic assessment of the patellofemoral joint after SPN and IPN suggests minimal risk [5, 14], and several anatomical studies show similar articular damage between approaches [83–85]. The influence of nail removal (if it occurs) should also be considered, as removal is always performed via an infrapatellar incision, regardless of the initial approach [86].

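### Item 2 of the anterior knee pain question does not say which operation it means, so a patient with persisting pain after nail removal can be scored as having none

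*Protocol article*

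**What the plan says.** Protocol article, Primary clinical outcome measure, sets out three Yes/No questions for the participant:

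- Item 1: "Do you experience any pain in the knee of the leg that was operated on". This identifies the leg, not the operation.
- Item 2: "Was this pain present only after surgery and not beforehand". No operation is named.
- Item 3 asks whether the pain is at the front of the knee.

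The scoring rule is: "If patients answer yes to all questions, their pain will be regarded as postoperative AKP". A single No therefore means no AKP.

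Protocol deviations foresees a second operation on the same leg: "Indications for nail removal may include patient preference, knee pain, and infection". These patients stay under observation: "Patients that undergo nail removal will be asked to be followed up for an additional 18 months after nail removal". The Discussion adds: "The influence of nail removal (if it occurs) should also be considered". It also notes that removal is done through an infrapatellar incision in both arms.

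The authors themselves use the word surgery for the nailing. Trial design, for example, compares the two approaches "during the first 18 months after surgery".

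**The concern.** Once the nail has been removed, the patient has had two operations on that leg, and none of the three items tells them apart. The patients exposed are those whose AKP was bad enough to prompt removal and did not resolve. If such a patient takes item 2 to refer to the removal, No is a truthful answer, because the pain was there before it. The scoring rule then records no AKP.

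Two uses of the answer are affected. At 12 months it is the primary clinical outcome, analysed by logistic regression on surgical approach. AKP status is also the yardstick for the new tool, which "will be assessed on its ability to differentiate participants with and without AKP", with candidate measures ranked by area under the curve (AUC), sensitivity and specificity. An analysis plan can define the outcome, but it cannot change how the patient understood the question.

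**Working it through.** The plan gives no figure on this point to reproduce. The check has two parts: the logic of the item, and the size of the effect under stated assumptions.

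**Logic.** For a patient with current pain at the front of the operated knee whose nail has been removed, items 1 and 3 are Yes. Item 2 depends on the reading:

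| Pain began | Surgery read as nailing (intended) | Surgery read as removal |
|---|---|---|
| Before nailing | No | No |
| Between nailing and removal | Yes: AKP | No: scored no AKP |
| After removal | Yes: AKP | Yes: AKP |

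The readings differ only in the middle row, and there a true case is lost. The error runs in one direction.

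**Inputs.**
- 25 completers per arm (Sample size).
- AKP in 12/25 = 48% per arm. This is an assumption, chosen as the whole number nearest the 47% average cited in the Discussion (0.47 × 25 = 11.75).
- Number misclassified, k = 1, 2 or 3. This is also an assumption, since no removal rate or timing is given. Across 50 completers, 1 to 3 patients means that 2% to 6% have the nail removed for AKP, still have pain, and misread the item. Zero is also possible.

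**Effect on the arm comparison.** One patient is 1/25 = 4 percentage points. With no misreading, OR = 1.00, SE(log OR) = √(2/12 + 2/13) = 0.566, and the 95% CI is exp(±1.96 × 0.566) = 0.33 to 3.03. With k cases lost in one arm only:

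| k | Rate in affected arm | OR against 12/25 |
|---|---|---|
| 1 | 11/25 = 44% | (11/14)/(12/13) = 0.85 |
| 2 | 10/25 = 40% | (10/15)/(12/13) = 0.72 |
| 3 | 9/25 = 36% | (9/16)/(12/13) = 0.61 |

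If the same number is lost from each arm, the OR stays at 1.00 and both observed rates fall.

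**Effect on the tool.** Pool the arms: 24 true cases and 26 without AKP. Suppose a tool classifies every patient correctly, and k true cases carry the wrong label. Apparent sensitivity stays at 100%, apparent specificity is 26/(26 + k), and for a binary tool AUC = (1 + specificity)/2:

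| k (both arms together) | Apparent specificity | Apparent AUC |
|---|---|---|
| 1 | 26/27 = 96% | 0.98 |
| 2 | 26/28 = 93% | 0.96 |
| 3 | 26/29 = 90% | 0.95 |

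**The case against.** The strongest reply is that the misreading is remote. The nailing is the natural meaning in context, and the protocol uses the word that way throughout. For the 12-month outcome to be wrong, a patient must have the nail removed, for knee pain, before 12 months, still have the pain, and read the item as being about the removal. The protocol gives no frequency for any of these steps. All of this stands. It limits the size of the problem but does not remove the ambiguity. Later visits, at 18 months and after removal, are more exposed than the 12-month one.

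The article also shows the items without the headings or instructions of the online form, which might define the operation. That is possible, but the article presents these as the questions participants will be asked, and nothing in them or around them names the operation.

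Third, the planned data could help identify affected patients afterwards, since AKP is assessed at earlier visits and subsequent surgeries are recorded. This is partly right. It works only where AKP was recorded at a visit before the removal, and it is a repair that clearer wording would make unnecessary.

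Finally, rewording does not settle attribution. New pain caused by the infrapatellar removal incision would still count as AKP after the nailing, in both arms. That is true, but it is a separate question from which operation item 2 refers to.

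**Conclusion.** The point holds as a minor weakness in the wording of the primary clinical outcome. Under the printed items and the all-Yes rule, a patient with persisting nail-related AKP can truthfully answer in a way that scores as no AKP, and the error can only remove true cases. It lowers the observed AKP rate and makes a good tool look less specific, whichever arm the patients are in. It creates a spurious difference between the approaches only if such cases differ by arm.

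The size rests on assumed counts. One to three patients would move results by amounts well inside the sampling error of a 25-per-arm pilot, and the true number may be zero. The clinical analyses are declared exploratory and no criterion in Table 2 uses AKP, so the feasibility conclusions are untouched.

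**What to change.** In item 2, replace the word 'surgery' with 'the operation to insert the nail'. The meaning is unchanged for patients who keep the nail, so their answers already given remain comparable. If the online form already names the operation, it is enough to print that wording in the protocol.

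For patients with a removal who have already answered the present wording, check any No on item 2 against their AKP answers at earlier visits and their recorded subsequent surgeries.

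The cost is a few words in one questionnaire item, with no added patients, visits or forms. How nail removal enters the analysis is a matter for the SAP and is not part of this point.
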